### Qualitative program evaluation

To gain insights into (1) mechanisms and/or program features that contribute to any experienced effects of STAIRS and (2) the usability and acceptability of the program, patients’ perceived value of the STAIRS-training as a whole and of its different elements will be qualitatively evaluated. For this, semi structured in-depth interviews will be conducted by the coordinating researcher (DW; MSc, male, lecturer at a university of applied sciences and PhD candidate) with selected patients until data saturation is reached. We expect that approximately 15 patients are needed for this. Selection will be performed using maximum variation sampling based on age, sex, ethnicity and number of previous depressive episodes to create maximum variation [69]. The interviews will be held at home or another preferred location of the patient. It will take approximately 90 min and will address the following topics: perceived effects (in general, control, identity, social contact), meetings (in general, activities, trainers, peers, structure), homework assignments and the website used. In an iterative process, the interviews will be supplemented with preliminary results from the RCT and previously conducted interviews, allowing patients to reflect on previous findings. The collection of all qualitative data and reporting of the results will be guided by the COnsolidated criteria for REporting Qualitative studies (COREQ) [70].

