### Recruitment and randomization

Participants are recruited from October 2022 to June 2024 from several mental healthcare organizations in the North of the Netherlands (including the University Center of Psychiatry [UCP] from the University Medical Center Groningen [UMCG], Mental Health Services Drenthe [GGZ-Drenthe], and Dimence).

Patients can be included in the study if they are between 18 and 65 years old, receive treatment for MDD and have depressive symptom severity levels that have decreased to moderate or less, according to the Inventory of Depressive Symptomatology self-report (IDS-SR). Exclusion criteria are: a primary diagnosis of bipolar depression or depression with psychotic features, comorbid schizophrenia spectrum or other psychotic disorder, comorbid moderate or severe dependence on alcohol or drugs, and neurological disorders (e.g., dementia). Additionally, patients with insufficient command of the Dutch language, cognitive problems or indication of low IQ (i.e., < 80), who do not possess a computer or smartphone, and/or who have been referred to a different mental health service for other mental problems are excluded.

In the participating centres, treating clinicians will inform eligible patients about the study and provide contact information to the coordinating researcher (DW) when a patient is willing to participate. Also, information about this study will be shared on different social media platforms, allowing interested participants to contact the coordinating researcher themselves. Once a patient has expressed their interest in participating, a researcher will contact them to further explain the study and check eligibility. An information letter will be sent, and a patient will have a week to contemplate, after which they will be contacted again. When a patient is willing to participate, a meeting will be planned with a researcher to discuss any further questions and to sign an informed consent form.

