### Measurements

Quantitative data will be collected by administering online self-report questionnaires in the week prior to the intervention (T0; baseline), the week following the intervention (T1) and 6 months later (T2). Patients can complete the questionnaires at home. A reminder will be sent after three days, and contact will be made by telephone after a week to promote participant retention. In addition to the questionnaires, a short structured interview will be conducted at T2 to assess depressive relapse in the past 6 months. Qualitative data will be collected by conducting semi structured in-depth interviews with a selection of patients from the intervention group, immediately after the end of the STAIRS-program (T1). Figure 2 gives an overview of the planned enrolment, interventions and assessments.

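### Interviewed STAIRS patients are to be shown preliminary RCT results at T1, six months before their self-reported T2 outcome; this can shift T2 in one arm and opens outcome data before follow-up is complete

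*Protocol article*

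**What the plan says.** All references are to the protocol article.

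- **What is shown.** Under Qualitative program evaluation: "the interviews will be supplemented with preliminary results from the RCT and previously conducted interviews". Earlier interviews are named as a separate source, so the natural reading of the first source is quantitative trial data. The stated purpose, to let interviewees comment on what has been found so far, makes clear that the patients see it.
- **To whom and when.** Under Measurements, the interviews are held "with a selection of patients from the intervention group, immediately after the end of the STAIRS-program (T1"). No control patient is interviewed.
- **How many.** "We expect that approximately 15 patients are needed for this".
- **By whom.** "semi structured in-depth interviews will be conducted by the coordinating researcher". Under Recruitment and randomization, clinicians pass willing patients' details to the same person, and social media notices are used, "allowing interested participants to contact the coordinating researcher themselves".
- **Outcome schedule.** Under Measurements, data come from "online self-report questionnaires in the week prior to the intervention (T0; baseline), the week following the intervention (T1) and 6 months later (T2"), with a relapse interview added at T2.
- **Role of T2.** Under Quantitative analyses, the primary outcome is the change in recovery from T0 to T1 and from T0 to T2. Under Primary outcome measure, it is scored on the I.ROC, a self-report scale.

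**The concern.** The I.ROC asks patients for their own view of their recovery, including matters such as hope and self-esteem. Participants know whether they attended an eight-week group training or received letters. A patient who hears during follow-up how the trial is going may expect more, or less, of the program and answer the T2 questionnaires accordingly. The relapse interview also depends on the patient's own account.

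This exposure exists in one arm only. Randomization does not balance it, because it arises after allocation. The planned regression of change on treatment group cannot separate it from the effect of the program.

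A second issue is access. To present trial results in the interviews, the coordinating researcher must have them. That person is also the contact point for referrals and, under Data management, one of two people with access to the file linking identifiers to patients. Results would therefore be known to someone close to enrolment before the trial's follow-up is complete.

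**Working it through.** **1. Timing.** The interview takes place at the end of the program and T2 falls six months after T1. Every interviewed patient, including the last one enrolled, therefore still owes T2 data when interviewed. Any trial result shown must come from an incomplete trial, whatever the pace of recruitment. The Economic evaluation section labels the six-month follow-up T1, which conflicts with Measurements. Since Measurements ties the interview to the end of the program in words, the order stands.

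**2. Overlap with recruitment.** Study design calls the trial concurrent, and recruitment runs from October 2022 to June 2024. Overlap is therefore likely, but no sentence states it.

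**3. The plan's own figures.** Power calculation: 2 × ((1.96 + 0.84) / 0.5)² = 62.72, so 63 per group and 126 in total; 126 / 0.9 = 140, or 70 per group. This reproduces. The values d = 0.5 and 70 per group (63 after dropout) are the yardsticks below.

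**4. Size of a possible shift.** The article gives no figure for the effect of disclosure. Assume a shift s in exposed patients, in SD units of the outcome, with s from 0.1 to 0.5.

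- Exposed share, at most: 15 / 70 = 0.214 (21%).
- Shift in the STAIRS mean at T2 = s × 15 / 70.
- Share of the planned effect = shift / 0.5.

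| s (assumed) | Shift in arm mean | Share of d = 0.5 |
|---|---|---|
| 0.1 | 0.021 SD | 4% |
| 0.3 | 0.064 SD | 13% |
| 0.5 | 0.107 SD | 21% |

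If all 15 are among 63 STAIRS patients who remain, the share is 15 / 63 = 0.238. The shifts are then 0.024, 0.071 and 0.119 SD (5%, 14% and 24% of 0.5).

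**5. Consequence for the T2 test, as illustration.** With no true effect and a normal approximation, SE = √(2/70) = 0.169 SD. The two-sided rejection rate is Φ(shift/SE − 1.96) + Φ(−shift/SE − 1.96). It is about 0.067 for s = 0.3 and 0.097 for s = 0.5, instead of 0.05. With 63 per arm the values are 0.069 and 0.103. These rates come from a displaced mean, not from looking at the data more than once. A downward shift gives the same rates, and would also mask part of a true benefit.

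**The case against.** The strongest reply is that the article states a procedure, not a bias.

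- **Content is undefined.** The results shown could be pooled, or T1 summaries for STAIRS patients alone. This stands: a reader might infer repeated looks at the comparison between arms, but no passage mentions results by arm. No stopping or adaptation rule depends on these results either, so looking does not by itself inflate type I error.
- **Exposure may be smaller.** The earliest interviews may have few or no results to show. This stands: 15 of 70 is an upper figure.
- **Direction is open.** Neutral or unfavourable results could lower expectations. This stands: the shift falls in one arm only, but it need not favour STAIRS.
- **Recall window.** The I.ROC covers the past three months and T2 is six months after T1, so the interview lies outside the window. This makes a large shift less plausible. It does not rule one out, because an altered expectation can outlast the interview.
- **Recruitment is protected.** An assistant from outside the study allocates from a random list in order of consent, and the article does not say that the coordinating researcher checks eligibility or takes consent. This largely stands: biased recruitment might be inferred, but the article shows no route from knowing results to a distorted comparison.
- **T1 is hardly touched.** A reader might infer that the T1 questionnaire is affected too, because its order relative to the interview is not given. That is operational detail which a condensed article may leave to the full protocol, so it is no finding.

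None of this removes the core: the article says that trial results will be shown to patients in one arm whose self-reported primary outcome is not yet complete.

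**Conclusion.** The concern holds as a risk that the stated procedure creates. What the text establishes is that preliminary RCT results go into interviews with STAIRS patients only, that each of them still has T2 to complete, and that the interviewer is the person who receives referrals. It does not establish that T2 will be biased, that any shift would favour STAIRS, or that results will be open during recruitment.

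The size rests on two assumptions: that all of about 15 interviewees are exposed, which is an upper limit, and that their T2 scores shift by 0.1 to 0.5 SD, which has no source in the article. On these, the T2 arm mean moves by about 0.02 to 0.11 SD, or 4% to 21% of the planned effect. The T0 to T1 half of the primary outcome is probably little affected. A modest risk of this kind is still worth removing, since removal costs little and an exposure cannot be undone.

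**What to change.** - In Qualitative program evaluation, strike the mention of preliminary trial results, so that interviews build only on themes from earlier interviews.
- State that no RCT outcome results are shown to participants whose T2 is pending.
- State that outcome results by arm stay closed to recruiting staff, including the coordinating researcher, until the last T2 is in.
- Integrate the qualitative and quantitative findings after that point.

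The cost is a short wording change and a rule on data access that someone has to keep. Interviewees can no longer comment on interim trial figures. The mixed-methods aim survives, because the two strands can be merged at the end.

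A T2 analysis without the interviewed patients is not a useful addition. It would remove a purposively chosen, post-randomization subset from one arm. It would also run against the rule under Quantitative analyses that nobody is excluded, and it could not separate disclosure from selection or from the interview itself.

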### Data management

A data management plan (DMP) is created and made available on DMP online. Data will be collected and managed according to the General Data Protection Regulation (GDPR; in Dutch: Algemene Verordening Gegevensbescherming) and applicable codes of conduct, such as the research code of the UMCG. Confidentiality of participant data will be secured by removing all identifiable data and replacing it with a unique identifier. Only the principal investigator and coordinating researcher will have access to the key file that links the unique identifier to the identifiable data. During the trial, all data will be stored on the research drive of the UMCG. After the trial, the data will be stored for a minimum of 15 years in a secured study-specific folder on the research drive of the UMCG. The deidentified data will be made accessible upon request after the latter is assessed by the principal investigator.

### Ethical statement

All procedures of this study will be conducted in accordance with the principles of the Declaration of Helsinki (latest version 19 October 2013) and in accordance with the Dutch Medical Research Involving Human Subjects Act (WMO). This study was approved by the Medical Ethical Committee (METc) of the UMCG (no2021/357). The study has been registered on ClinicalTrials.gov under trial number NCT05440812.

### Statistical analysis

#### Power calculation

Based on previously conducted meta-analyses on the effect of psychosocial interventions [71], behavioural activation treatment [72] and supported internet-based treatment [73] on the social functioning of patients with depression, a medium effect size is expected. The sample size estimation for the RCT was based on a Cohen’s d of 0.5, a *p*-value cut-off (alpha) of 0.05 (Z_alpha_ 1.96) and a power (1-beta) of 80% (Z_beta_ 0.84). The following calculation was used to obtain the number of needed participants per group (n_gr_): N_gr_ = (SD_gr1_ + SD_gr2_/ratio) * ((Z_alpha_ + Z_beta_)/d)^2^, where the ratio between the two groups’ sample sizes (n_gr1_/n_gr2_) was set to 1 (equal group sizes). This calculation resulted in (1 + 1/1) * ((1.96 + 0.84)/0.5)^2^ = 2 * 31.4 = 62.8) an estimated 63 participants needed per group (total sample size = 126). With an expected dropout rate of 10%, we arrived at a total required sample size of 140 ((126/9)*10), with 70 participants per treatment group.

### Data analysis

#### Quantitative analyses

Before the start of the analyses, any missing values will be imputed 20 times using a fully conditional specification [74]. After multiple imputation, all analyses will be conducted in each of the 20 datasets and pooled across imputed datasets [75]. No subjects will be excluded in any phase of the data preprocessing and analyses. All analyses will be conducted according to the intention-to-treat (ITT) principle, and findings will be reported following the Consolidation of the Standards of Reporting Trials (CONSORT) guidelines [76].

The primary outcome in this study is the change in the level of subjective experienced recovery during the intervention period (T0 to T1) and at the six-month follow-up (T0 to T2). The efficacy of the STAIRS-training will be examined by comparing the change in recovery scores between the intervention group and the control group using linear regression models with the treatment group (0 = control; 1 = intervention) as the main independent variable. In subsequent analyses, subgroup differences in the change in the primary outcome will be explored by testing the interaction effects of treatment condition with a range of baseline covariates: age, gender, marital status, employment status, level of education, family composition, number of previous depressive episodes, duration of current depression, first age of onset, and sleeping problems. Intervention effects on the continuous secondary outcomes are analysed using the same approach as for the primary outcome. To investigate the effect of treatment on the relapse rate (during follow-up; T1 to T2), logistic regression will be used with relapse at T2 (1 = yes; 0 = no) as the outcome and the treatment group as the independent variable.

For all estimated linear regression models, assumptions of conditional normality, linearity and homoscedasticity will be checked by inspection of Q‒Q plots and residual plots. In case of assumption violations, outcome variables will be transformed (e.g., natural logarithm) and models rerun. If necessary, different transformations will be applied until the model assumptions are met. Imputation and statistical analyses will be conducted with SPSS and/or R. A two-sided alpha level of 0.05 will be used.

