To address this gap, the training program ‘Storytelling and Training to Advance Individual Recovery Skills’ (STAIRS) [45] was developed by a project team (consisting of clinical professionals and experts by experience). In the STAIRS program, all of the above-described elements are integrated. Furthermore, the program is designed to foster the mechanisms that were concluded to be supportive of recovery in a recent systematic review [46]: (1) provision of information and teaching skills, (2) promotion of a working alliance, (3) the use of role modelling and (4) increasing choice and opportunities. To evaluate the STAIRS program’s efficacy in improving recovery, we aim to conduct a randomized controlled superiority trial (RCT) among MDD patients, who are in symptomatic remission. The intervention group will receive STAIRS training on top of care as usual (CAU). The comparison group will receive CAU and basic written psychoeducation about the recovery process. The primary quantitative outcome of the RCT is a measure of functional and personal recovery. Secondary outcomes include measures of depressive symptom severity, experienced control over life and cost-effectiveness. In exploratory quantitative analyses, potential demographic moderators of responding to the STAIRS-training will be investigated. Our primary hypothesis is that patients assigned to the STAIRS group will reach a significantly higher level of functional and personal recovery than the patients assigned to the comparison group. In addition, we hypothesize that the STAIRS group will show: (1) lower symptom severity and relapse rates in the first six months following the intervention, (2) lower levels of depression-related functional disabilities, (3) higher levels of perceived empowerment, (4) higher levels of perceived control of events and ongoing situations, (5) higher levels of perceived self-management skills, and (6) lower costs per quality-adjusted life year (QALY) compared to the comparison condition.

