### Interventions

All patients who are included in the RCT will continue to receive CAU according to applicable clinical guidelines during the complete runtime of the study. CAU can consist of psychotherapeutic and/or drug treatment, outpatient, day or inpatient treatment and individual or group treatment.

The main goal of the STAIRS program is to increase the level of functional and personal recovery of patients suffering from the lasting impact of depression on their lives. This will be done with different exercises, by sharing experiences and by providing supportive information. The STAIRS training has a duration of eight weeks, in which participants address the following themes in weekly group sessions: effects of depression and treatment, structure, public stigma and self-stigma, self-image, meaningfulness, connecting to others, relaxation and preventing relapse. Each session will be guided by a clinician (psychologist, nurse practitioner or medical social worker) and a certified expert by experience. Trainers will undergo a 1-day train-the-trainer where the aim of the program and the working methods used are discussed, the complete program is reviewed and example exercises are practised. In between sessions, participants can keep working on a theme via homework assignments on which they will be asked to reflect and interact with each other in a private online community.

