### Primary outcome measure

#### Recovery

As STAIRS was developed to support recovery beyond clinical recovery, we chose subjective experienced recovery as the primary outcome measure, which entails both functional and personal recovery. This will be measured with the Individual Recovery Outcome Counter (I.ROC) [50], which is a self-report questionnaire specifically developed to measure the subjective experienced recovery of patients. It focuses on four domains of well-being: (1) home, (2) opportunity, (3) people and (4) empowerment. Each domain consists of 3 recovery aspects, which are described with several keywords and a single question to indicate the level of this aspect in one’s life during the last three months (on a 6-point Likert scale ranging from ‘never’ to ‘always’). The I.ROC sum score of all items (range 12–72) will be used to measure the level of recovery, with higher scores indicating better recovery. The domains focused on by the I.ROC cover both aspects of functional recovery (e.g., everyday skills, movement and being active, social network) and personal recovery (e.g., meaning and life goals, self-esteem, hope for the future). The I.ROC has been shown to have good internal consistency with a Cronbach’s alpha of 0.86 and was found to be a preferred recovery measurement tool by patients compared to two other commonly used recovery measures [50].

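### Two primary time points share one unadjusted alpha of 0.05 with no rule for success, while the sample size covers a single comparison

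*Protocol article*

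**What the plan says.** The Quantitative analyses section of the protocol article makes the primary outcome the change in "recovery during the intervention period (T0 to T1) and at the six-month follow-up (T0 to T2"). The arms are compared on these changes "using linear regression models with the treatment group (0 = control; 1 = intervention) as the main independent variable". The only statement on error control closes the same section: "A two-sided alpha level of 0.05 will be used".

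The primary hypothesis in the Background names no time point. It reads: "patients assigned to the STAIRS group will reach a significantly higher level of functional and personal recovery than the patients assigned to the comparison group".

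Under Power calculation, "The sample size estimation for the RCT was based on a Cohen’s d of 0.5", with alpha 0.05 (Z = 1.96) and 80% power. The result is 63 per group, or 140 in total after 10% dropout. That section also names no time point and makes no allowance for a second primary test.

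Three further statements bear on the choice of time point:

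- Each I.ROC item refers to the patient's "life during the last three months" (Primary outcome measure).
- "The STAIRS training has a duration of eight weeks" (Interventions).
- T0 falls in the week before the programme, T1 in the week after it, and T2 six months later (Measurements).

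**The concern.** Two changes are primary, each can give its own treatment estimate and p-value, and nothing says how the two results combine into a verdict on the trial. The rule matters because the two obvious candidates fail in different ways. If a significant result at either time point counts, the chance of a false positive primary claim exceeds 5%. If both must be significant, the chance of success under the planned effect is below 80%. A split result, positive at one time point and not at the other, has no meaning fixed in advance, and the choice of emphasis would then be made with the data in view.

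The two time points also differ in what the primary instrument measures. At T1 part of the I.ROC recall period lies before the programme started; at T2 none of it does. This bears on which time point should come first.

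**Working it through.** **Inputs.** From Power calculation: d = 0.5 (SD 1), two-sided alpha 0.05, power 80%, equal groups, 10% dropout. From Quantitative analyses: two primary changes and one alpha. The correlation r between the two test statistics is not given. It is assumed, and a range is shown.

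**1. The plan's own figure.** n per arm = 2 × ((1.96 + 0.84) / 0.5)² = 2 × 31.36 = 62.7, rounded up to 63. Total 126, and 126 / 0.9 = 140. Both stated figures reproduce, for one test at 0.05.

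**2. Success if either time point is significant.** Family-wise error = 1 − P(|Z1| < 1.96 and |Z2| < 1.96) under the null, with Z1 and Z2 bivariate normal with correlation r. For r = 0 this is 1 − 0.95² = 0.0975.

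| Assumed r | Family-wise error |
|---|---|
| 0 | 9.75% |
| 0.5 | 9.1% |
| 0.7 | 8.3% |
| 0.9 | 7.0% |

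It exceeds 5% at every correlation below 1.

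**3. Success only if both are significant.** Assume d = 0.5 at both times. The expected test statistic at 63 per arm is 0.5 / √(2/63) = 2.806. Power for one test is Φ(2.806 − 1.96) = Φ(0.846) = 80.1%. Joint power is P(Z1 < 0.846 and Z2 < 0.846) with correlation r.

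| Assumed r | Joint power |
|---|---|
| 0 | 64% |
| 0.5 | 69% |
| 0.7 | 71% |
| 0.9 | 75% |

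**4. What the remedies cost in patients.**

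- Splitting alpha (0.025 per time point): 77 per arm, 154 evaluable, and 154 / 0.9 = 171.1, so 172 recruited. At 63 per arm, power per time point falls from 80.1% to 71.4%.
- One primary time point, with the other tested only after it: the first test stays at 0.05, so 63 per arm and 140 in total stand.

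**5. Recall window.** Take three months as 13 weeks and assume the eight weekly sessions run without a break. T1 then falls 8 to 9 weeks after the programme starts. The part of the T1 window before the start is 13 − 9 = 4 to 13 − 8 = 5 weeks, that is 4/13 = 31% to 5/13 = 38%. At T2, six months after T1, the last three months lie wholly after the programme.

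**The case against.** The strongest reply is that the article never says each change is tested at 0.05 as a separate route to success. It gives one general alpha, it condenses a fuller protocol, and multiplicity rules are often left to an analysis plan that is not shown here. The error inflation also needs an either-counts rule that the text does not state. This stands in part: the separate tests are inferred from the plural models and the single alpha, and an unseen plan could add a rule. It does not remove the point, because the article itself fixes two primary changes, an unadjusted alpha and a sample size for one comparison. These do not fit together under either rule.

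A second reply concerns recall. Both randomised arms answer the same I.ROC with the same look-back, so the overlap favours neither arm. That is right. A reader might go further and infer that the T1 effect shrinks in proportion to the overlap, derive a much lower T1 power, and dismiss a null T1 result as an artefact. The documents do not support this. It requires patients to weight all 13 weeks equally, which nothing in the article says, and it treats the planned d of 0.5 as an undiluted I.ROC effect. The article takes that value from meta-analyses of social functioning. The overlap may attenuate the T1 contrast, but by how much cannot be computed.

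Third, the power calculation does not favour T2 over T1, since it names neither. This also stands: the preference for T2 rests on the recall window alone.

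**Conclusion.** The point holds. With two primary changes, one unadjusted alpha and a sample size for a single comparison, the stated 5% error and 80% power cannot both apply to the primary outcome. The family-wise error is about 7% to 9.75% if either result suffices, over assumed correlations from 0.9 down to 0. Joint power is about 64% to 75% if both are needed, over correlations from 0 to 0.9 and with d = 0.5 at both times. The correlation is an assumption, but the direction of each conclusion does not depend on it.

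The recall overlap at T1 (4 to 5 of 13 weeks before the programme) follows from the article's own schedule. It is a reason to put T2 first. It is not evidence that the T1 comparison is invalid.

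**What to change.** Name one time point as the single primary comparison of I.ROC between arms at two-sided 0.05, and test the other at 0.05 only if the first is significant. The fixed order keeps the family-wise error at 5% and preserves the planned power for the first test. T2 is a reasonable first choice for the reason given above; T1 first would fit the sample size equally well. Write the chosen time point into the primary hypothesis and the power calculation too. Give it in months as well as by label, because the Economic evaluation section calls the six-month follow-up T1.

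Settle this before any outcome data by arm are seen. The Qualitative program evaluation section foresees preliminary trial results being brought into the interviews, so the change should come before any such results are prepared.

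Leave the I.ROC recall instruction as it is. Rewording it to cover the time since the previous questionnaire would alter the instrument in a trial that has been recruiting since October 2022. It would also give T1 and T2 recall windows of different length, and T0 has no previous questionnaire to refer to.

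The cost is a change of wording in the protocol, the registration and the analysis plan; the 140 patients are unchanged. The one real downside is that an effect seen only at the gated time point can no longer be claimed as the primary result.

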After informed consent is obtained, patients will be randomly allocated to one of the study arms. Randomization will be performed at the patient level by a research assistant who is not involved in the study, using simple randomization with a 1:1 allocation ratio. A list with 140 randomly generated numbers (0 or 1) will be used to allocate patients in order of the date and time of the informed consent meeting. Patients who are randomized to the active intervention condition will be placed on a waiting list for the treatment in (a) the organization where they received all their previous treatment (for patients referred from organizations that offer the STAIRS training) or (b) in the UCP (for patients who are referred from organizations that do not offer the STAIRS training). The STAIRS training starts when at least three patients have been added to the waiting list. At that time, patients will receive an email inviting them to join the training. This email will contain all needed information about the date and location of the meetings and how to access the private online environment that is used as part of the STAIRS-program. When attending physical meetings turns out to be difficult for participants in the intervention condition, they will be given the option to follow the STAIRS training online. Previous pilot work showed this to be a usable and acceptable option [45].

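### The primary model compares I.ROC change scores with no stated baseline term; adding the T0 score as a covariate would gain precision at almost no cost

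*Protocol article*

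**What the plan says.** All references are to the protocol article.

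- **Outcome.** Quantitative analyses defines the primary outcome as the change in I.ROC from T0 to T1 and from T0 to T2.
- **Model.** Efficacy is tested "by comparing the change in recovery scores between the intervention group and the control group using linear regression models". Treatment, coded 0 or 1, is described as the main predictor. No baseline I.ROC term is named.
- **Covariates.** Ten baseline characteristics are listed, but only for exploratory moderation: "subgroup differences in the change in the primary outcome will be explored by testing the interaction effects of treatment condition with a range of baseline" variables. Baseline I.ROC is not among the ten. The section on sample characteristics allows that baseline information might serve as covariates, again to study how person characteristics affect the STAIRS effect.
- **Secondary outcomes.** "Intervention effects on the continuous secondary outcomes are analysed using the same approach as for the primary outcome".
- **Allocation.** Patients are allocated "using simple randomization with a 1:1 allocation ratio". No stratification is described.
- **Power.** The calculation uses a "Cohen’s d of 0.5" with both SDs set to 1. It does not say whether this is the SD of the score or of the change.

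**The concern.** Subtracting the baseline is the same as adjusting for it with a slope fixed at 1. I.ROC is an imperfectly reproducible self-report score, so the regression of follow-up on baseline would usually have a slope below 1. The subtraction then over-corrects: an arm that by chance starts low is credited with some regression to the mean. Averaged over randomisations this cancels, but it adds noise to the estimate.

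At stake is precision on the primary outcome at both time points and on every continuous secondary outcome. The T0 scores that would recover it are already collected.

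**Working it through.** **Inputs from the protocol article (Power calculation, Quantitative analyses).** d = 0.5, two-sided alpha 0.05, power 80%, SDs of 1, 63 per arm, 10% dropout, 140 in total.

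**Assumed, not in the documents.** The correlation r between T0 and follow-up I.ROC, taken as 0.3, 0.5 or 0.7, and equal SDs at T0 and follow-up.

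**1. The plan's own figure.** 2 × ((1.96 + 0.84)/0.5)² = 2 × 31.36 = 62.7, so 63 per arm and 126 in total. 126/0.9 = 140. The stated size reproduces. Power at 63 per arm is 80.1% by the normal approximation and 79.5% by the noncentral t. The noncentral t is used below.

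**2. General condition.** Let s0 and s1 be the SDs at T0 and follow-up, and let b = r × s1/s0 be the true slope.

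- Variance of change: s1² + s0² − 2·r·s0·s1
- Variance after baseline adjustment: s1²(1 − r²)
- Difference: s0²(1 − b)²

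The difference is zero only if b = 1. With s0 = s1 = 1 the variances are 2(1 − r) and 1 − r², and their ratio (adjusted to change) is (1 + r)/2.

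**3. Variance and power at 63 per arm.**

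| r | Var change | Var adjusted | Reduction | Power, d on score SD: change / adjusted | Power, d on change SD: change / adjusted |
|---|---|---|---|---|---|
| 0.3 | 1.40 | 0.91 | 35% | 65% / 83% | 80% / 93% |
| 0.5 | 1.00 | 0.75 | 25% | 80% / 90% | 80% / 90% |
| 0.7 | 0.60 | 0.51 | 15% | 95% / 97% | 80% / 86% |

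For d on the score SD, the standardised effect is 0.5/√Var. At r = 0.3 this is 0.5/1.183 = 0.423 for change and 0.5/0.954 = 0.524 adjusted. For d on the change SD, the adjusted effect is 0.5/√((1 + r)/2). At r = 0.3 this is 0.5/0.806 = 0.620. Put as sample size, 63 × (1 + r)/2 means the adjusted model would need 41, 48 or 54 per arm to match what the change analysis delivers with 63.

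**4. Sensitivity to imbalance.** The SE of the baseline difference is √(2/63) = 0.178 score SD, with a 95% range of ±1.96 × 0.178 = ±0.35. Given an observed baseline difference D, the change-score estimate is displaced by −(1 − r)D.

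| r | Shift at 1 SE | Shift at the 95% limit | 95%-limit shift as a share of 0.5 score SD |
|---|---|---|---|
| 0.3 | 0.12 SD | 0.24 SD | 49% |
| 0.5 | 0.09 SD | 0.17 SD | 35% |
| 0.7 | 0.05 SD | 0.10 SD | 21% |

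Steps 3 and 4 describe the same loss. The excess variance 2(1 − r) − (1 − r²) equals (1 − r)², which is the variance contributed by the uncorrected imbalance. They should not be counted as two separate harms.

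**5. The equal-SD assumption.** With s1/s0 = 1.25 and r = 0.6 (both assumed), b = 0.75. The change variance is 1.5625 + 1 − 1.5 = 1.0625, against an adjusted variance of 1.5625 × 0.64 = 1.00. The ratio is 1.06, where the equal-SD formula 2/(1 + r) would give 1.25. The gain can therefore be smaller than the tables show.

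**The case against.** **The wording does not exclude baseline adjustment.** Treatment is called the main independent variable in the linear models, whereas the relapse model simply has treatment as its independent variable. The Discussion also promises methods for grouped data that the analysis section omits, so that section is evidently condensed, and a SAP not shown here may add the covariate. This stands as a caution: a reader should not infer that the plan forbids adjustment. But the article does fix the response and the main predictor, and nothing in it commits to a baseline term.

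**A reader might infer that the trial is underpowered.** This is not supported. The 65% at r = 0.3 arises only if d = 0.5 is on the score SD. The article gives a unitless d and defines the outcome as change. If d is on the change SD, the planned analysis has its 80% at every r.

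**A reader might infer that the estimate is biased or driven by imbalance.** This is not supported either. Under randomisation the change-score estimate is unbiased and its test keeps its nominal level. The larger shifts in step 4 need an imbalance at the 95% limit; a typical one moves the estimate by 0.05 to 0.12 SD. Simple randomisation matters little here, because stratifying would not balance I.ROC unless I.ROC itself were a stratification factor.

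**The loss is not universal.** It vanishes if the true slope is 1, and at r = 0.7 on the score-SD reading it is only 95% against 97% power.

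The point does not extend to the relapse model, whose outcome is not a change score.

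**Conclusion.** The point holds as a recommendation on efficiency. The stated analysis is valid and the sample size need not change. It does give up precision that the collected data could provide, on the primary outcome and on all continuous secondary outcomes. Under equal SDs and r between 0.3 and 0.7, the variance that could be removed is 35% to 15%. The gain in power at 63 per arm is about 13 to 6 percentage points if d is on the change SD, and about 18 to 2 points if it is on the score SD. The direction is firm for any slope other than 1. The size rests on an r and an SD ratio that the documents do not give.

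**What to change.** State that the T1 and T2 models for I.ROC include the T0 I.ROC score as a covariate, and that the model for each continuous secondary outcome includes that outcome's own T0 score. Fix this before the outcome data are analysed. Change can remain the reported outcome: once T0 is in the model, the treatment estimate is identical whether the response is the change or the follow-up score. It would also help to say which SD the d of 0.5 refers to.

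The cost is about one sentence and one extra term per model, with no new data. The adjusted model relies on T0 being unaffected by knowledge of allocation, which matters because T0 is taken just before the intervention, after randomisation. The change score relies on the same condition, so adjustment adds no new dependence.
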